## **6. Study procedures and visits**

Each person must be fully informed prior to being enrolled to the clinical trial. Eligible subjects have to be informed in person by the investigator and in writing by the patient information. Only after clarification of all questions this person is asked to sign two copies of the consent form and date by hand. Then a copy of patient information and informed consent of the eligible person shall be issued; the second copy of the consent form is kept in the ISF.

### **6.1 Schedule of assessment**

| CHRONOGRAM                                                          | Pre-Screening  | Screening   | Inclusion/
randomization | BM
withdrawal | Baseline
Treatment | Tracking (M = months) |            |             |              |              |
|---------------------------------------------------------------------|----------------|-------------|-----------------------------|------------------|-----------------------|-----------------------|------------|-------------|--------------|--------------|
| PROGRAMMING
OF VISITS:                                           | Day -60/-46    | Day -45/-41 | Day -45/-31                 | Day -45/-31      | V0                    | V1                    | V2         | V3          | V4           | V5           |
|                                                                     |                |             |                             |                  | Day 0                 | M1 (+/- 7)            | M3 (+/- 7) | M6 (+/- 14) | M12 (+/- 30) | M24 (+/- 30) |
| Instructions for wash-out 48 hours NSAIDs a washout      |                | X           |                             |                  | X                     | X                     | X          | X           | X            | X            |
| Prohibition of NSAIDs a                                  |                |             |                             |                  | X                     | X                     | X          | X           | X            | X            |
| Instructions for wash-out 24 hours painkillers b washout |                | X           |                             |                  | X                     | X                     | X          | X           | X            | X            |
| Delivery of the Information sheet                                   | X              |             |                             |                  |                       |                       |            |             |              |              |
| Signature of Informed Consent form                                  |                | X           |                             |                  |                       |                       |            |             |              |              |
| General medical History and Demography                              |                | X           |                             |                  |                       |                       |            |             |              |              |
| Lumbar related medical history                                      |                | X           |                             |                  |                       |                       |            |             |              |              |
| Vital signs c                                            |                | X           |                             | X                | X                     | X                     |            | X           | X            | X            |
| Physical Exploration                                                |                | X           |                             | X                | X                     | X                     |            | X           | X            | X            |
| RX of Lumbar Spine Simple and Dynamic                               |                | X           |                             |                  |                       |                       |            |             |              |              |
| ECG 12-Lead                                                         |                | X           |                             |                  |                       |                       |            |             |              |              |
| Blood sampling for routine laboratory testing and urine analysis    |                | X           |                             | X                | X                     | X                     | X          | X           | X            | X            |
| Urine pregnancy test                                                |                | X           |                             |                  |                       |                       |            |             |              |              |
| Preceptive Viral Serologies                                         |                | X           |                             |                  |                       |                       |            |             |              |              |
| Checking inclusion and exclusion criteria                           |                | X           |                             |                  |                       |                       |            |             |              |              |
| Randomization                                                       |                |             | X                           |                  |                       |                       |            |             |              |              |
| Pain lumbar spine (VAS), ODI, SF-36                                 | X              | X           |                             | X                | X                     | X                     | X          | X           | X            | X            |
| Lateral MRI, T2, quantitative                                       | X d |             |                             |                  | X                     |                       |            | X           | X            | X            |
| Adverse Events                                                      |                |             |                             |                  | X                     | X                     | X          | X           | X            | X            |
| Concomitant medication                                              |                | X           |                             | X                | X                     | X                     | X          | X           | X            | X            |

a: NSAIDs washout of at least 2 days before screening, inclusion and baseline. NSAIDs will not be authorized during the first 6-month after baseline. However, if needed after the first 6 months, NSAIDs could be used

b: Patients will be required to refrain from taking paracetamol or opioids within 24 hours of each clinical visit for efficacy evaluations

c: vital signs: Temperature, heart rate, arterial blood pressure, height, weight

d: MRI was also used to assess the Pfirrmann and Griffith's score

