#### **3.1 Inclusion criteria**

- Age between 18 and 65 years.
- Signed informed consent.
- Symptomatic chronic LBP due to moderate IDD [modified Pfirrmann score 3-4 (Pfirrmann et al., 2001), Griffith score 3-7(Griffith et al., 2007)] at max.3 levels of the lumbar spine unresponsive to conservative treatment, physical and medical for at least 6 months. Physical treatment includes physiotherapy. Medical treatments includes NSAID, paracetamol, opioids and myorelaxant. (For more details, see paragraph 1.1.4).
- Annulus fibrosus intact, demonstrated by MRI.
- Pain baseline > 40 mm on VAS (0- 100).NSAID washout of at least 2 days before screening.
- NSAID washout of at least 2 days before screening.

- Painkillers washout of at least 24 hours before screening.
- For females of childbearing potential (see definitions in paragraph 6.5), a negative pregnancy test must be documented at Screening.
- Men and women should use effective contraception during treatment and for at least 24 months after BM-MSD discontinuation. The complete list of contraceptive methods is described in the patient information sheet and in the paragraph 6.5. As a precautionary measure, breast-feeding should be discontinued during treatment with BM-MSD and should not be restarted after discontinuation of BM-MSD.

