### **5.5 Application of the cells**

Material Preparation: Cells tend to aggregate during transport, therefore, prior to application, this effect will be compensated by subjecting the syringe to a gentle oscillating movement allowing the cells to resuspend.

Patient Preparation: It will be verified that the informed consent document, the preoperative tests, and the medical history (that may be of interest during the procedure) are available. An antibiotic prophylaxis will be performed. The prophylaxis is the following: 2g Cefazolin, 1/2 hour before injection. Or in case of allergy: Clindamycin 900 mg (1/2 h before injection). The antibiotic solution is to be delivered intravenously (IV).

**Patient positioning:** The patient will be placed on a radiolucent surgical table and Wilson frame in a lying prone position. Once the patient is installed, the C-arm mobile radioscopy system will be positioned and tested and the skin prepped.

**Intradiscal cellular injection procedure:** The injection will be done by fluoroscopy. The investigator enters the images amplifier in the field. The adequate point of entry into the disc will be assessed by fluoroscopy and marked on the skin. The local anaesthesia will be infiltrated. The tip of the needle will advance until it punctures the disc and penetrates the nucleus pulposus. Controls will be carried out in anteroposterior and lateral planes to check the correct position of the needle, prior to the infusion of the cell suspension. After removing the needle mandrel, the syringe will be screwed to the needle and the cellular suspension (2ml containing  $15 \pm 1 \times 10^6$  MSC) will be slowly injected, stopping temporarily if the pain is exacerbated. A small Mepore dressing will be put into place.

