### **6.2.2 Screening visit**

- Signature of Informed Consent Form.
- Checking inclusion and exclusion criteria.
- Demographics and general medical history.
- Lumbar related medical history (includes past history of osteoarthritis, osteoporosis, lumbar pain, injury, trauma, fractures, surgical procedure or other conditions).
- Medication history therapy and unresponsive (including physical therapy) for at least 6 months.
- Vital signs after sitting for at least 5 minutes, (temperature, blood pressure, and heart rate, height, weight).
- Musculoskeletal physical exploration.
- Lumbar spine examination (X ray).
- Pain assessment of the lumbar spine by visual pain scale (VAS, Oswestry Disability Index ODI in order to measure a patient's permanent functional disability, Quality of life assessment using SF-36.
  - Instruction for wash out (NSAIDS washout of at least 2 days before the screening Visit, no painkillers 24h before the screening visit) will be given to the patient after written informed consent.
- If clinical and radiological criteria fulfilled, perform ECG (12-lead)
- Blood sampling for routine laboratory testing
  - Haematology: haematocrit, haemoglobin, RBC, WBC; PC
  - Biochemistry: Electrolytes, Creatinine, BUN, ALT, AST, AP, Bilirubin, Coagulation (INR, PTT)
  - CRP
- Urinalysis (dipstick): Glucose, Ketones, blood, protein, nitrite, leucocytes, , bilirubin in urine
  - Urine pregnancy test in woman of childbearing

potential

- Blood sampling for preceptive viral serologies
  - HBs antigens
  - Anti-HBc antibodies
  - Anti-HCV antibodies
  - Anti-HIV-1 and anti-HIV-2 antibodies, Anti HV1 gp41
  - Anti-HTLV-1, HTLV-2 antibodies
  - Wasserman testing
  - Blood testing for Syphilis serology
- Concomitant medication

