### **6.2.3 Inclusion visit and randomization**

- Confirm inclusion and exclusion criteria
- Randomization

Randomization procedure: the randomization is performed 24 hour-a-day online by the central randomization web-service customized by the sistem. To randomize a patient, investigators have to login, enter the patient identification, additional checks and factor values. The person in charge of cell injections will be strictly forbidden from discussing treatment allocation with patients and clinical observers.

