### **6.2.4 BM-MSc Withdrawal**

#### **- Prior to Bone Marrow cells extraction:**

- Physical exploration
- Vital signs (Temp, BP, HR)
- Blood sampling for routine laboratory testing

Haematology: haematocrit, haemoglobin, RBC, WBC; PC

Biochemistry: Electrolytes, Creatinine, BUN, ALT, AST, AP, Bilirubin, CRP

- Urinalysis (dipstick): Glucose, Ketones, blood, protein, nitrite, leucocytes, bilirubin in urine

- Pain assessment of the lumbar spine by visual pain scale (VAS, Oswestry Disability Index in order to measure a patient's permanent functional disability, Quality of life assessment using SF-36
- An antibiotic prophylaxis will be performed. The prophylaxis is the following: 2g Cefazolin, 1/2 hour before injection. Or in case of allergy: Clindamycin 900 mg (1/2 h before injection). The antibiotic solution is to be delivered intravenously (IV).
- Concomitant medication (analgesic medication with diary file)

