### **6.2.5 Day 0 - Visit 0: Visit baseline and treatment**

- Physical exploration
- Vital signs (Temp, BP, HR)
- Lateral MRI, T2, quantitative
- Medication history therapy
- Blood sampling for routine laboratory testing
- Urine analysis

- Pain assessment of the lumbar spine by visual pain scale (VAS)
- Oswestry Disability Index in order to measure a patient's permanent functional disability, Quality of life assessment using SF-36
- Instruction for wash out (NSAIDS washout of at least 2 days before this screening Visit, no painkillers 24h before the visit)
- Prohibition of NSAIDs
- Adverse event assessment
- Concomitant medication
- Intervention : injection of autologous cells or sham procedure (under fluoroscopy guide and monitor cell implantation). The affected disks (max 3) are treated simultaneously once only, at the V0 visit and no subsequent doses are expected.

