## **6.5 Contraceptive methods**

Adult subjects of childbearing potential (ACBP) must:

- Understand the potential teratogenic risk to the unborn child and the need for effective contraception.
- Be capable of complying with effective contraceptive measures.
- Be informed and understand the potential consequences of pregnancy and the need to notify her study doctor immediately if there is a risk of pregnancy.
- Understand the need to commence the study treatment as soon as study drug is dispensed following a negative pregnancy test.
- Understand the need and accept to undergo pregnancy testing based on the frequency outlined in this protocol.
- ACBP enrolled in this protocol must agree to use two reliable forms of contraception simultaneously or to practice complete abstinence from heterosexual contact during the following time periods related to this study: 1) while participating in the study; 2) in case of dose interruptions; and 3) for at least 24 months after the last dose of study drug.
- The two methods of reliable contraception must include one highly effective method and one additional effective (barrier) method. ACBP must be referred to a qualified provider of contraceptive methods if needed. The following are examples of highly effective and additional effective methods of contraception.

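### The only scheduled pregnancy test is at Screening, so it is at least 41 to 45 days old at the once-only injection; no test is listed at Day 0.

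*Protocol*

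**What the plan says.** **Where the test is scheduled.** Protocol 6.1 has a row for "Urine pregnancy test" marked once, in the Screening column (Day -45/-41). Section 6.2.2 lists "Urine pregnancy test in woman of childbearing" potential at that visit. Section 3.1 requires that "a negative pregnancy test must be documented at Screening".

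**What the later visits list.** The inclusion visit (6.2.3, Day -45/-31) asks the site to "Confirm inclusion and exclusion criteria" and to randomize. The marrow visit (6.2.4) adds a urine dipstick covering "Glucose, Ketones, blood, protein, nitrite, leucocytes, bilirubin in urine". Day 0 (6.2.5) lists a urine analysis and then the intervention: "injection of autologous cells or sham procedure (under fluoroscopy guide and monitor cell implantation"). The affected discs are treated once, with no further dose. None of these three visits lists a pregnancy test, and neither do V1 to V5.

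**Other text that bears on it.** Section 6.5 asks women to "Understand the need to commence the study treatment as soon as study drug is dispensed following a negative pregnancy test". Section 5.5 has the team verify that "the informed consent document, the preoperative tests, and the medical history" are available before the cells are applied. Section 3.2 excludes pregnant women, advises ruling out pregnancy after a late period, and promises an additional test once relevant exposure has ended. Section 3.5 withdraws a patient who becomes pregnant.

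**The concern.** The protocol treats pregnancy as a bar to treatment. It is an exclusion criterion (3.2) and a reason for withdrawal (3.5), and patients must understand a possible risk to a fetus (6.5). Yet the only test comes about six weeks before a single injection that cannot be undone. Day 0 is the last point at which a pregnancy begun since Screening could change the decision to treat.

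The interval is built into the product. Marrow is taken after inclusion, and the cells are passaged at days 14 and 21 of culture (5.1). Section 6.2.4 also allows a second aspiration if cells are contaminated, delayed in shipping or too few. That would lengthen the interval, and no retest is attached to it.

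**Working it through.** **Inputs.** From 6.1: Screening at Day -45 to -41, inclusion and marrow withdrawal each at Day -45 to -31, treatment at Day 0. From 2.1: two arms of 26. From 6.2.2 to 6.2.10: the contents of each visit.

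**Age of the test at dosing.** Day 0 minus screening day:
- shortest: 0 - (-41) = 41 days
- longest: 0 - (-45) = 45 days

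This is the nominal interval; a repeat aspiration would add to it.

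**Age of the criteria re-check at dosing.** Day 0 minus inclusion day: 0 - (-31) = 31 days to 0 - (-45) = 45 days. The re-check in 6.2.3 is thus at least 31 days old at the injection, and it carries no test.

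**Tests by visit.**

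| Visits | Number | Pregnancy tests listed |
|---|---|---|
| Screening | 1 | 1 |
| Inclusion, marrow, V0 | 3 | 0 |
| V1 to V5 | 5 | 0 |

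**Could the urine analysis at V0 already include it?** The documents treat the two as separate. Section 6.1 gives them different rows, 6.2.2 lists both as distinct items, and the dipstick contents in 6.2.2 and 6.2.4 do not include a pregnancy test.

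**Does other text require a repeat before Day 0?**
- 6.5 links the start of treatment to a negative test but sets no interval, so it can be met by the Screening result.
- 5.5 verifies that preoperative tests are available. It names no pregnancy test and asks for no new one.
- 3.2 makes the check after a late period a recommendation, and only in that event.
- 3.5 acts on a pregnancy that has been recognised.

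None mandates a test.

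**Who is exposed.** Under 5.6, control patients have no disc injection and the C-arm is not running. Exposure to cells and fluoroscopy therefore concerns women of childbearing potential among the 26 patients planned for the active arm. The protocol does not say how many women that will be.

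**The case against.** The strongest case against is that the protocol does not rely on one test. Section 6.5 requires two simultaneous contraceptive methods or abstinence throughout participation. It also requires the patient to tell the study doctor at once if there is a risk of pregnancy, so the trigger is risk and not a confirmed pregnancy. Section 3.2 excludes premenopausal women without acceptable birth control, 6.2.3 re-checks the criteria, and 3.5 lets the investigator withhold the cells to prevent harm. All of this stands and lowers the risk. None of it detects a contraceptive failure that the patient has not noticed, which is what a test is for.

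A second objection is that 6.5 may already imply a test close to dosing. That reading is possible. A reader might go further and infer that the protocol requires such a test and the schedule merely forgot it. The text does not support that: 6.5 gives no interval, and neither 6.1 nor 6.2.5 schedules a test. On either reading the remedy is the same.

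Third, the number at risk is smaller than the trial. This is right, and 52 must not be read as the number exposed.

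**Conclusion.** The point holds as a gap in safety scheduling that should be fixed. The only mandated pregnancy test is nominally 41 to 45 days old at a once-only injection, and none of the three visits after Screening, up to and including dosing, lists one. This rests on the 6.1 day windows being kept and on reading the visit lists as complete.

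Several stronger readings should not be drawn:
- **Expected pregnancies or fetal harm.** The protocol gives no number of women of childbearing potential and no pregnancy rate, and 1.6 reports no preclinical sign that cells migrate systemically.
- **No contraception before dosing.** One sentence in 3.2 starts contraception at treatment, but the same bullet excludes women without acceptable birth control and 6.5 covers the whole of participation. No interval is left uncovered.
- **The V5 window.** A test at V5 could fall up to 30 days before Month 24, but nothing says that the additional test in 3.2 marks the end of contraception, so this is no defect.
- **Analysis.** Sample size and analysis are not affected.

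Two minor wording faults stand beside the main point and do not add to its weight. The additional test in 3.2 (repeated in the synopsis) has no date and no visit, although 6.5 binds women to the testing frequency that the protocol sets. The male contraception rule in 6.5 ends at the same undated point, whereas 3.1 asks for at least 24 months.

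**What to change.** **Main change.** In 6.1 and 6.2.5 add: urine pregnancy test at V0, before the procedure, for women of childbearing potential in both arms; a negative result is required to proceed. Testing both arms keeps the blind.

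**Minor changes.** In 3.2 and its synopsis copy, tie the additional test to a named follow-up visit, and add it to 6.1 and to that visit's list. In 6.5, align the male contraception duration with the 24 months in 3.1.

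**Cost.** One urine strip per eligible woman at V0, where urine is already collected. The ceiling is 2 x 26 = 52 strips plus replacements, even if every patient qualified; the post-dose test adds at most as many again. The eCRF and patient information would probably need a small update, and if the change is judged substantial it must be submitted under 13.3.4. The real downside is that a positive result at V0 in the active arm wastes an expanded cell batch. A patient withdrawn at that point is replaced under 3.8.

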## **6.2 Visits during the course of the trial**

### **6.2.1 Pre-Screening visit**

- Delivery of the Information sheet.
  - Lateral MRI, T2, quantitative.
  - Pain assessment of the lumbar spine by visual pain scale (VAS, Oswestry Disability Index ODI in order to measure a patient's permanent functional disability, Quality of life assessment using SF-36.

